## Abstract

**Background:**

Most older adults do not adhere to the US Centers for Disease Control physical activity guidelines; their physical inactivity contributes to overweight and multiple chronic conditions. An urgent need exists for effective physical activity-promotion programs for the large number of older adults in the United States.

**Objective:**

This study presents the development of the intervention and trial protocol of iCanFit 2.0, a multi-level, mobile-enabled, physical activity-promotion program developed for overweight older adults in primary care settings.

**Methods:**

The iCanFit 2.0 program was developed based on our prior mHealth intervention programs, qualitative interviews with older patients in a primary care clinic, and iterative discussions with key stakeholders. We will test the efficacy of iCanFit 2.0 through a cluster randomized controlled trial in six pairs of primary care clinics.

**Results:**

The proposed protocol received a high score in a National Institutes of Health review, but was not funded due to limited funding sources. We are seeking other funding sources to conduct the project.

**Conclusions:**

The iCanFit 2.0 program is one of the first multi-level, mobile-enabled, physical activity-promotion programs for older adults in a primary care setting. The development process has actively involved older patients and other key stakeholders. The patients, primary care providers, health coaches, and family and friends were engaged in the program using a low-cost, off-the-shelf mobile tool. Such low-cost, multi-level programs can potentially address the high prevalence of physical inactivity in older adults.

## Introduction

The benefits of regular physical activity on the well-being of older adults are well established. Even small increases in physical activity at a population level could have far-reaching positive impacts on chronic diseases such as diabetes, cardiovascular diseases, and several cancers [1-3]. The US Centers for Disease Control and Prevention and the American College of Sports Medicine have recommended 150 minutes of moderate-to-vigorous physical activity (MVPA) per week [4]; however, less than 5% of American older adults adhere to the guideline [5-7]. Physical inactivity is associated with high prevalence of overweight (60%) and chronic conditions (80%) in this population [8]. As the elderly population continues to grow—13% of the US population will be older than 65 years of age by 2020 [8]—an urgent need exists for physical activity-promotion programs that can reach a large population of older adults efficiently.

Increasing older adults’ physical activity, especially MVPA, is challenging. Literature suggests that effective physical activity-promotion programs are those built upon social and behavioral theories and practices, extend beyond the individual-level factors, and incorporate social and health care support [9-11]. When promoting physical activity in older adults, multi-level intervention programs that promote physical activity through goal setting and tracking at the individual level, social support at the interpersonal level, continuous monitoring at the health care level, and positive social norms at the community level are more likely to have sustainable effects [10-13].

More than 67% of older Americans (65 years or older) use the Internet and 42% own a mobile phone [14]; the digital divide in older adults has narrowed in the past decade [15]. The high rates of owning mobile tools suggest feasibility of mobile-based physical activity interventions. Mobile-based programs can reach a large number of patients efficiently; such programs can be easily tailored to individual needs and integrated into the health care system where electronic health records (EHRs) have been widely adopted [16-18]. In fact, a growing number of mobile-based, physical activity-promotion programs have been developed and tested in older adults [19,20]. However, recent reviews of existing programs have shown inconclusive evidence. While some studies report significant efficacy, others suggest minimal benefits, especially compared to usual care [20,21]. These programs, which typically used simple texting or short message service (SMS) text messaging to deliver reminders, had only short-term effects [22,23]. Some programs have required participants to use newly developed websites or mobile apps, thus limiting the population reach [10,21]. Despite inconclusive evidence from mobile-based, physical activity-promotion programs, reviews of existing literature have revealed some common characteristics of successful physical activity programs. They typically (1) incorporate the patient as an active participant in goal setting and tracking, (2) are based on behavioral and socioecological theory, (3) emphasize problem solving and the use of social support, and (4) provide both proactive and follow-up support [3,10,24]. Literature also documents the importance of social support, especially support from friends and family in mobile-based, physical activity-promotion programs [25].

Older adults tend to have more trust in their primary care providers (PCPs), or *general practitioners* in some countries, compared to other populations [26]. American older adults see their PCPs at least every 6 months [27]. Thus, the primary care clinics provide an ideal setting for delivering physical activity-promotion programs to older adults. Many PCPs, however, do not counsel their patients for physical activity promotion; they either have to address other medical complaints raised by the patients or they see no necessity of bringing up physical activity in the consultation with patients [28]. Our recent interviews with PCPs found that most physicians assumed patients understood the importance of physical activity and the lack of regular physical activity was due to patients’ insufficient motivation [29,30]. A recent BMJ systematic review identified only 15 trials conducted in primary care organizations and the most typical intervention was a one-time simple counseling session by a PCP or nurse [13]. More research is therefore needed to explore the efficacy of theory-guided, physical activity-promotion programs in primary care settings.

We aim to address the literature gaps noted above by proposing a multi-level, mobile-enabled, physical activity-promotion program called *iCanFit 2.0* in a primary care setting. Guided by socioecological theory, the iCanFit 2.0 program incorporates PCPs and health coaches in behavioral goal setting and continuous support for the patients. The intervention will exert effects at the individual, interpersonal, health care, and community levels. Mobile tools will facilitate patient-provider communication, enhance motivation, and provide ongoing feedback and social support to promote physical activity, as shown in Figure 1. To test the efficacy of iCanFit 2.0, we also designed a cluster randomized controlled trial (RCT) in a large health care organization.

## Methods

### Development of iCanFit 2.0

#### Overview

The development of the iCanFit 2.0 program was based on the following data sources and processes: (1) Preliminary studies with older adults in primary care settings and mHealth interventions including the iCanFit Web app, (2) qualitative interviews with older patients in a primary care clinic prior to this design, and (3) iterative discussions with stakeholders.

#### Preliminary Studies

From 2011 to 2015, we conducted the following formative research and mHealth interventions on physical activity promotion among older adults:

Assessment of overweight patients’ barriers to physical activity from the perspectives of PCPs. Through online surveys with 57 PCPs and focus groups with 49 PCPs, we learned that PCPs were aware of the importance of counseling older patients regarding physical activity and identified lack of motivation and social support as major barriers to regular physical activity [28-30].Use of the iPod Touch for patient health behavior assessment and patient-provider communication. We developed an app on the iPod Touch—before the iPad was released—so patients could complete a brief health behavior assessment (HBA) on a touch screen while waiting for appointments with a PCP. A colorful chart report was generated instantly (see Multimedia Appendix 1). When the patient walked into the appointment with a PCP, the report became a natural conversation starter and facilitated patient-provider communication and collaborative goal setting. We piloted this app with 109 patients in a primary care clinic and the results showed that 30% of the participants reported that their PCP discussed the report with them, 24% established behavioral goals with him or her as a result of the discussion, and 90% related positive experiences with using mobile tools to generate an HBA report [31].Development and testing of the iCanFit interactive website for older adults. With the goal to promote physical activity in older cancer survivors, we developed an interactive website called iCanFit. We conducted three phases of research: formative research with key stakeholders [32], usability testing of the website with target users [33], and an efficacy trial with older cancer survivors [34]. The users of iCanFit reported high levels of usefulness and satisfaction. Participants reported a higher level of quality of life (effect size=0.35) and a higher level of physical activity (effect size=0.45) following the use of the iCanFit Web app [34].

#### Qualitative Interviews With Older Diabetes Patients in a Primary Care Clinic

The initial design of iCanFit 2.0 was the combination of the HBA tablet app and the interactive iCanFit Web app. As the initial design of iCanFit 2.0 evolved, we conducted qualitative interviews with 103 older diabetes patients in a primary care clinic. Considering most older adults have multiple chronic conditions, our preliminary studies focused on different chronic conditions to ensure that iCanFit 2.0 can serve the needs of a large number of older adults. The mean age of the participants in the qualitative interviews was 50 years and the mean years of living with diabetes was 10 years. Most of these older patients used the Internet and more than half had a mobile phone. They had positive attitudes toward a mobile-based, physical activity-promotion program and offered many suggestions and concerns for the design of iCanFit 2.0.

#### Iterative Discussions With Key Stakeholders to Refine the Design

After 10 years working in healthy aging and chronic disease management, we have established rapport with local communities and health care organizations; we have also always engaged key stakeholders in the intervention design, implementation, and evaluation. In designing iCanFit 2.0, we had a series of group discussions with our key stakeholders. We brought our initial design to the meeting and obtained their feedback; the iterative process continued until a satisfactory protocol was agreed upon by all key stakeholders. The current design of iCanFit 2.0 reflects the inputs from our target patients and other key stakeholders and is substantially different from the original design.

### Community Engagement

Prior to completion of protocol design and project implementation, a Community Advisory Board (CAB) will be established, consisting of older patients, community leaders, health care providers, and administrators. At least five members of the CAB will be older patients. The CAB will have 10 members and vote on a director and a secretary. The CAB will meet with the project team every month in the first 6 months of the project and every 6 months afterward. The CAB will offer gatekeeper and stakeholder concerns as well as recommendations on program design, feasibility issues, implementation, and evaluation strategies; it will also help the research team interpret findings and advise on how to translate research findings into sustainable programs.

### Intervention Trial

#### Overview

The intervention trial compares the effectiveness of the iCanFit 2.0 intervention program with a comparator program among overweight older adults in a primary care setting. To achieve this goal, we will conduct a cluster RCT in 12 family medicine clinics (six pairs) in Central Texas, USA. In each pair of comparable clinics, one will be randomized to the intervention group and one to the control group (see Figure 2).

**Figure 1 figure1:**
[figure not shown]
Theoretical framework of the multi-level intervention, iCanFit 2.0.

**Figure 2 figure2:**
[figure not shown]
Intervention trial flowchart.

#### Study Sites and Sources of Patients

We will conduct the proposed trial in 12 family medicine clinics that belong to a large university-affiliated, integrated health care system in Central Texas. These clinics were selected because of their similarity in patient demographics, clinic operation, and service coverage. The 12 clinics will be grouped into six pairs. Clinics in each pair have been selected to have similar characteristics of size (ie, number of patient visits per year) and number of overweight older adults as well as situated miles apart to reduce possible contamination of the intervention. We will use a randomization table to assign the two clinics in each pair into the intervention group or the control group.

#### iCanFit 2.0 Intervention Protocol

As illustrated in Figure 3, the iCanFit 2.0 intervention protocol includes four steps. First, after the eligible participants complete the informed consent forms, they will complete an HBA on an iPad (see Multimedia Appendix 1 for sample screenshots), which takes about 15 minutes. Right after completion, patients will receive a printed copy of the HBA summary report with colorful charts of their current level of physical activity compared to the recommended physical activity levels (see sample summary reports in Multimedia Appendix 1). Meanwhile, the same report will be printed out in the office of the PCP with whom the patient has an appointment. Second, the patient brings the HBA report into his/her appointment with the PCP and the report serves as a natural conversation starter to facilitate patient-provider communication and joint goal setting. Third, right after the patient’s appointment with the PCP in the primary care clinic, a health coach will meet with the patient, further explain the HBA report, and ensure the patient has set a long-term physical activity goal, if the patient has not set one with the PCP. The health coach will give the patient a Fitbit Flex 2 (Fitbit Inc) (see Multimedia Appendix 2 and section below about the device) and demonstrate how to use the device. The health coach will also help the patient to create an account on the iCanFit online community. The health coach will advise on how to set short-term (eg, weekly) goals, track and sync data, share progress with family and friends via Facebook, and obtain personalized feedback on the iCanFit online community. The counseling session will last 30 minutes; a photo-illustrative brochure with instructions on how to use the Fitbit as well as account information and reminders will be given to the patient. Fourth, the health coach will constantly monitor patients’ use of the Fitbit and iCanFit online community. Patients will receive incentives (eg, online badges, virtual coins, and honor levels) for meeting physical activity goals and updating their progress. Any questions posted on the iCanFit online community will be answered by the health coach within 12 hours. If a patient is “idle” for 2 weeks, the health coach will call the patient to offer help and address the patient’s barriers. Patients will also receive a brochure of safety tips (see Multimedia Appendix 3), which details possible adverse events during exercise and how to take action depending on the situation. For adverse events that need immediate medical attention, patients are advised to go to the nearest emergency room. For nonurgent matters, they can contact the health coach, who can assist with scheduling a clinic appointment with the patient’s PCP.

**Figure 3 figure3:**
[figure not shown]
Process of iCanFit 2.0 intervention. PCP: primary care provider.

**Figure 4 figure4:**
[figure not shown]
Process of comparator protocol (for patients in the control group). PCP: primary care provider.

#### Comparator

The patients in the control group will receive usual care enhanced with a Fitbit Flex 2, as shown in Multimedia Appendix 2. The Fitbit Flex 2 was released in 2016, costs US $75, and weighs a quarter of an ounce. It is compatible with iPhones and Android phones, only needs to charge once a week, syncs automatically with mobile phones within 20 feet, and easily syncs to a computer with a USB port. It tracks steps taken, stairs climbed, calories burned, distance travelled, and sleep time. Figure 4 illustrates the process of the comparator protocol. After eligible patients provide informed consent, they will first complete an HBA on an iPad while waiting for their appointment. Unlike patients in the intervention group, patients in the control group will not receive any reports from their HBA; after their appointment with the PCP, they will receive a Fitbit Flex 2 and a brochure explaining how to use the Fitbit and the benefits of regular physical activity. Patients in the control group will not be given any information about the iCanFit online community; neither will they receive counseling or monitoring from health coaches. Similar to the intervention group, control group patients will receive the safety tips of exercise brochure.

#### Recruitment of Patients

Eligibility of participants includes the following: (1) 60 years of age or older, (2) body mass index (BMI) of 25 kg/m^2^ or higher, (3) have no medical condition prohibiting regular physical activity as shown in the EHR, (4) have access to the Internet through a computer or mobile phone, and (5) have a phone that can receive SMS text messages or phone calls. Based on our prior experience of recruiting participants for mHealth interventions in primary care settings and the consideration of minimal interruption of daily operation of the clinic, we will recruit participants as follows: in the EHR system, patients who are 60 years of age or older, have a BMI of 25 kg/m^2^ or higher, and have no medical condition that prohibits them from exercise will be *flagged*. When a flagged patient checks in for his/her appointment, a health coach will be notified, who will approach the patient and explain the purpose of the project and check if the patient meets all the criteria. Eligible patients will be invited to participate in the study. Participation is completely voluntary; if the patient declines to participate, we will take notes regarding the patient’s demographic information for future analysis. If the patient agrees to participate, she/he will complete the informed consent form and be able to begin the study at the very visit when they are recruited. In case some patients agree to participate but cannot start the study at that visit, we will schedule another visit for these patients to start the study within a month.

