#### Power and Sample Size Calculations

The primary outcome of the study is the total minutes of MVPA per week. MVPA is measured as “very active” and “fairly active” on Fitbit. The secondary outcome of the study is the patient’s self-report quality of life, measured by the 12-Item Short Form Survey [39]. We hypothesize the effect size of the iCanFit 2.0 to be 0.25, based on a prior Fitbit intervention trial [43]. Following the procedure developed by Cohen, the calculation of sample size is carried out in three steps by assuming a .05 significance level to achieve the power of 0.8 [44]. First, we assume that two independent samples can be obtained for the same size *n*_1_ each. Then the total sample size is *n*=2 x *n*_1_. In this ideal scenario, the total sample size *n*=398 is required to detect the effect size *d*=0.25 between the two population means. Second, because the randomization occurs at the clinic level, we need to consider the clustering effect. Previous similar research suggests a small clustering effect due to multiple patients per physician, but virtually no clustering effect between patients with different physicians in the same clinic [45]. We assume that if the intraclass correlation coefficient (ICC) per patient is equal to .05, and that ICC per physician is equal to 0, then equation 1 holds:

ICC=(1 + ICC_patient) x (1 + ICC_physican) – 1 = .05 (1)

Thus, the design effect is as follows in equation 2:

D=1 + (m - 1) x ICC (2)

where m is the average number of patients per physician in our effective sample. If we restrict m to be no more than 6, then D=1 + 5 x .05 = 1.25. We would need a sample size of 498 (ie, 398 x 1.25) after factoring in cluster effects. Third, based on our prior study of RCT primary care settings [36], we assume the attrition rate to be 0.2 after 12 months, thus the required sample size at baseline is 622 in total (ie, 498/[1-0.2]), or 52 patients per clinic on average. We will recruit no fewer than 30 and no more than 70 patients from each participating clinic.

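### Patients are recruited after clinic allocation by a health coach who knows the arm, so who joins may differ between arms, with no pre-intervention Fitbit value to show it

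*Protocol article*

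**What the plan says.** **Allocation.** Twelve clinics form six pairs. Study Sites and Sources of Patients says "We will use a randomization table to assign the two clinics in each pair into the intervention group or the control group", and Power and Sample Size Calculations repeats the unit: "because the randomization occurs at the clinic level".

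**Recruitment.** The health record flags patients by age, BMI and absence of a condition that rules out exercise. When a flagged patient checks in, "a health coach will be notified, who will approach the patient and explain the purpose of the project". Screening falls to the same coach, whose task is also to "check if the patient meets all the criteria". A consenting patient will "be able to begin the study at the very visit when they are recruited", or within a month if that is not possible. Demographic notes are kept on those who decline.

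**The coach's role by arm.** In intervention clinics, right after the appointment, "a health coach will meet with the patient, further explain the HBA report", hands over the Fitbit and holds a 30-minute session (iCanFit 2.0 Intervention Protocol). Control patients get a Fitbit and brochures after the appointment, and "neither will they receive counseling or monitoring from health coaches" (Comparator). That section also withholds the online community from control patients.

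**Numbers per clinic.** "We will recruit no fewer than 30 and no more than 70 patients from each participating clinic".

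**Analysis.** The Data Analysis Plan compares baseline characteristics descriptively by arm, adds background characteristics that it does not name, and tests the group-by-time coefficient, H0: α3 = 0.

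**The concern.** When clusters are randomised first and individuals are recruited afterwards by someone who knows the allocation, randomisation balances the clinics but does not protect the choice of patients within them. The two offers differ: a report, coaching, feedback and a community in one arm, a Fitbit and brochures in the other. If the recruiter's explanation reflects the offer at that clinic, different patients may accept. Motivation plausibly drives both acceptance and the primary outcome, weekly MVPA.

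An imbalance that arises this way is systematic, so enrolling more patients does not shrink it. The primary outcome cannot reveal it either, because Fitbit recording starts only after the arm-specific contact with the PCP has taken place.

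**Working it through.** **1. Does allocation precede recruitment, and does the coach know the arm?** The article says neither in so many words. Both follow from three statements read together:
- The clinic is the unit of allocation.
- The patient can begin at the recruiting visit, and the arm-specific steps (report or no report, coaching or none) take place at that visit. The clinic's arm must therefore be fixed by then.
- The coach counsels in one arm and does not in the other, so the coach cannot be unaware of the arm.

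**2. What do the existing safeguards cover?**

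| Safeguard | Covers | Leaves open |
|---|---|---|
| Flagging in the health record | Who is listed | How the study is explained, who agrees |
| Approach triggered by check-in | Order of approach | Same |
| Notes on decliners | Demographics | Motivation, activity |
| Baseline assessment with IPAQ (Table 1), before the appointment in both arms | Self-reported activity at entry | Fitbit MVPA, readiness to change |
| Background covariates | Whatever is chosen | IPAQ is not named |

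**3. How would a selection effect enter the stated test?** In equation 3 the expected difference between arms at time t is α1 + α3·t. Let recruitment add a constant difference c and a difference in trend s:

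- difference at time t = (α1 + c) + (α3 + s)·t

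The constant c goes into α1. The tested coefficient is biased by s, which arises if the arms differ in readiness to change. If the arms were instead compared on follow-up level (the hypothesis is worded as more MVPA per week), c would count in full.

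**4. Size.** The plan gives no figure for recruitment bias. Its sample size reproduces as follows: d = 0.25, α = 0.05 and power 0.80 give 198.52, so 199 per arm or 398 in total, with a one-sided t-test (two-sided would need 252 per arm, 504). Then 398 × 1.25 = 497.5, stated as 498; 498/0.8 = 622.5, stated as 622; 622/12 = 51.8, stated as 52 per clinic.

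As an illustration only, assume a shift b (in SD) in the contrast being tested, no true effect, and the effective 199 per arm in a simple comparison of two means:

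- SE = √(2/199) = 0.100
- one-sided false-positive risk = 1 − Φ(1.645 − b/SE)
- two-sided = 1 − Φ(1.960 − b/SE) + Φ(−1.960 − b/SE)

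| b (assumed) | b/0.25 | One-sided | Two-sided |
|---|---|---|---|
| 0 | 0% | 5% | 5% |
| 0.05 | 20% | 13% | 8% |
| 0.10 | 40% | 26% | 17% |

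These rates apply to a shift in whatever is tested. They cannot be read as the effect of an equal difference at entry on the test of α3.

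**The case against.** **The test is an interaction.** A constant difference at entry is absorbed by α1, so setting 0.05 to 0.10 SD at entry against d = 0.25 does not describe the planned test. This stands. What remains is selection on trajectory, whose size is unknown.

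**An imbalance would be visible.** Both arms complete the IPAQ after consent and before the appointment, and a baseline comparison by arm is planned. This stands in part. A reader might infer that selective recruitment could not be told apart from an intervention effect; that is too strong. But the IPAQ is self-report and does not measure readiness to change.

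**Much is already standardised.** Approach is triggered by check-in, consent precedes the assessment in both arms, the criteria left to the coach (internet and phone access) are factual, and all research staff share two months of training (Program Fidelity). This stands. None of it fixes what patients are told before they agree.

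**Scripts belong in the full protocol.** The article's silence on a script is not in itself an error. The point rests on what the article fixes: the order of events and the role of the recruiter.

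**The range of 30 to 70 shows nothing.** Pairs are matched on size, and unequal numbers are not selective enrolment. This stands; the range only leaves room for uneven recruitment.

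**Recruiting at the visit is deliberate.** It is chosen for minimal disruption and scalability. That is a fair reason to keep it, and the remedy below does.

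**Conclusion.** The point holds as a risk of identification or recruitment bias after cluster allocation. It rests on two close inferences: that allocation precedes recruitment and that the coach knows the arm. The size cannot be derived from the document. The illustrative shifts of 0.05 to 0.10 SD are assumptions and apply only to a shift in the tested contrast.

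Three stronger readings are not supported. A reader might infer that the randomisation is undone, but nothing shows that selection will occur. A reader might infer that the coach takes consent, but the article has the coach approach, explain and screen, and names no role for consent. A reader might also infer that the same coach always recruits and then treats a patient; the text allows this in intervention clinics but does not state it.

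**What to change.** 1. Use one recruitment script and one consent text in all 12 clinics, neutral as to allocation. They should not name the online community, because the Comparator section withholds it from control patients; a text describing both packages in full would conflict with that.
2. Keep the planned order of consent, then baseline assessment, and give no arm-specific information until both are complete.
3. Log flagged, approached, eligible and consented patients by clinic, and compare the proportions and the available characteristics by arm.
4. Prespecify baseline IPAQ activity, age and BMI as covariates in the primary multi-level model. Entered as main effects they adjust mainly the level; to bear on α3 they would also need interactions with time. Adjustment therefore supports the neutral script and does not replace it.

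The cost is slightly more paperwork: common wording and a log. IPAQ and age are already collected, and BMI is known from eligibility screening. The article reports the trial as not yet funded, so the change can be made before recruitment. The coach still knows the arm, so the bias is reduced, not removed.
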